**Table 2 Tab2:** **Time measurements**

**Week**	**0**	**1**	**2**	**3**	**4**	**5**	**6**	**7**	**8**	**9**	**10**	**11**	**12**	**13**	**14**	**15**	**24**
Measurement	**T0**-baseline	**T1**											**T2**				**T3**
Mate section	xx												xx				x
EQ–5D	xx												xx				x
DASS	xx												xx				x
Mini-plus	xx												xx				x
Blood	xx						x						x				
Urine	xx						x						xx				x
Medical consult	2x	2x	2x	x	x			x			x		x	x	x		
Baclofen (mg)	0	15–30	45– 60											30–45	30–15	15–0	0
Baclofen Side effect	x	2x	2x	x	x			x			x		x				
VAS	xx	x	x	x	x			x			x		xx				x
DDQ	xx	x	x	x	x			x			x		xx				x
Baclofen withdrawal checklist														x	x	x	
Timeline follow back													xx				x

xx = baclofen group and control group TAU only.

x = baclofen group.

T0 = end of GHB detoxification.

T1 = start baclofen treatment.

T2 = follow-up TAU only and end of baclofen therapy.

T3 = follow-up baclofen group.

### Statistical analyses

Descriptive analysis will be executed for all measurements and will include the mean, SD and frequencies of events with confidence intervals. Descriptive statistics will be used to compare the basic characteristics of the participants in the experimental group and the control groups. To assess any difference in relapse rates between the experimental group and the control groups (TAU group and matched historical group) at 3 month after detoxification Pearson Chi-squared test will be used for the dichotomous abstinence rates. ANOVA will be carried out on continuous variables, such as the total number of abstinent days, the maximum duration of continued abstinence, time before relapse (relapse defined as ≥ 3 times GHB use per day, for 2 subsequent days), and level of substance use over a period of 3 months. At 6 months period participants who continued baclofen will be compared to those who have stopped with baclofen (after 3 month) on relapse into GHB abuse or abstinence corrected for craving. The numbers of patients maintaining abstinence will be analysed with the intention-to-treat principles. The difference in craving will be analysed by MANCOVA at 3 months between groups (abstinent experimental versus abstinent TAU or relapsed TAU) with DDQ and VAS craving as dependent variables and corrected for craving levels immediately after detoxification. The change in craving in time during the baclofen treatment will be analysed via repeated measures MANOVA. By means of MANCOVA at 6 months after detoxification the difference in craving among participants who are still using baclofen and those who have discontinued baclofen will be analysed corrected for craving after 3 months. The effect of baclofen on the psychiatric symptoms levels (DASS, MINI) and also quality of life (EQ–5D) will be analyzed similarly as for craving at 3 and 6 months. The effects of the different TAU approaches as potential confounders will be tested in a sensitivity analyses (changing one-factor-at-a-time) in an linear regression including TAU per center as covariates.

Safety of baclofen, as assessed by the number and intensity of reported side effects, will be analyzed in the following categories: acceptable or unacceptable adverse effect, clinically significant deterioration, and relocation. In all analyses socio-demographic characteristics such as age and gender will be considered as co-variates in the analysis. Two-sided p-value of > .05 is considered statistically significant. The statistical software package SPSS will be used for all the computations.

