## Methods and Design

### Study design

The design is of an open label non-randomized controlled clinical study in six addiction care facilities in the Netherlands. The study is part of the Dutch national GHB Monitor 2.0 and data collection will take place between May 2014 and December 2015. After successful detoxification of GHB, patients will receive either baclofen on top of treatment as usual (TAU + baclofen) or treatment as usual (TAU) only. Assignment is based on in- and exclusion criteria and on patient preference (informed consent).

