### Participants

#### Recruitment

Participants are GHB dependent patients in treatment for detoxification at six participating addiction care facilities. These GHB dependent patients will be informed by their physician about the possibility to participate in the current study before GHB detoxification. The physician will inform the research nurse per centre on potential participants for the study, who will provide further study information to the patients after the detoxification. After informed consent, a research physician will perform the medical screening. The intervention group will be compared with two control groups: recently detoxified GHB dependent patients included in the Dutch national GHB Monitor 2.0, but that do not want to use baclofen (TAU only); and a matched historical control group from our previous work on GHB dependence (n = 274) of whom follow-up data are available [20]. The historical control group will be matched on age, gender, GHB use (dose and years), and number of detoxification attempts.

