The current study does have several limitations. First, the study is not randomized, nor placebo controlled. However, we will compare patients receiving baclofen with a control group matched for gender, age and the pattern of GHB use, in order to control for potential confounding factors. Second, the accompanying treatment as usual (TAU) is not identical in all participating addiction care facilities. This may confound our results. The impact of TAU will be checked with a sensitivity analysis compare patients’ results from the different centers conforming the add-on baclofen effect.

Given these methodological limitations the current study should be considered explorative in nature. Given the currently rather limited information from both preclinical and clinical studies of GHB such an explorative approach seems justified. We would also like to test the GHB substitution effect of baclofen (as a GABA-B agonist) hypothesis. It is important to evaluate of this effect is clinically recognized and obvious for the participants, and may define placebo use as non-beneficial. We need to be able to determine the margins of the required treatment dose. All forgoing justify this setup of an open label trail before a large placebo controlled randomized trial.

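### The only test named for 3-month abstinence, a Pearson chi-squared test between self-selected groups, cannot carry the promised covariates, and the matching offered against confounding does not cover the concurrent TAU group

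*Protocol article*

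**What the plan says.** All references are to the protocol article.

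- **Allocation (Study design).** The trial is open label and non-randomised. "Assignment is based on in- and exclusion criteria and on patient preference (informed consent" is the rule given.
- **Controls (Recruitment).** There are two control groups. The concurrent one consists of recently detoxified patients in the GHB Monitor, "but that do not want to use baclofen (TAU only". For the other, "The historical control group will be matched on age, gender, GHB use (dose and years), and number of detoxification attempts". No matching is described for the concurrent group.
- **Main test (Statistical analyses).** Relapse is compared "between the experimental group and the control groups (TAU group and matched historical group) at 3 month after detoxification", and a "Pearson Chi-squared test will be used for the dichotomous abstinence rates". Baseline characteristics of the groups are compared descriptively.
- **Covariates (same section, near its end).** "In all analyses socio-demographic characteristics such as age and gender will be considered as co-variates in the analysis".
- **Other confounder work (same section).** "The effects of the different TAU approaches as potential confounders will be tested in a sensitivity analyses", using a linear regression with TAU per centre.
- **Stated remedy (Discussion).** After conceding that the study is neither randomised nor placebo controlled, the authors write that "we will compare patients receiving baclofen with a control group matched for gender, age and the pattern of GHB use".

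**The concern.** People who choose baclofen may differ from people who refuse it in craving, anxiety, severity of GHB use and motivation. The Background itself lists craving, anxiety and depression among the reasons patients give for relapse. Where such factors are recorded at baseline, the main comparison should use them.

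The plan appears to offer three protections: covariates in all analyses, a matched control group and a sensitivity analysis of confounders. None of them, as written, reaches the 3-month abstinence comparison with the concurrent TAU group. A baseline imbalance in that comparison would be reported as part of the difference in abstinence, and a reader of the Discussion would believe that matching had dealt with it.

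**Working it through.** **1. Which safeguard reaches which comparison**

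| Safeguard in the plan | Baclofen vs concurrent TAU, 3-month abstinence | Baclofen vs historical controls, 3-month abstinence |
|---|---|---|
| Age and gender as covariates in all analyses | Not possible in a Pearson test; no other model named | Same, though both are matching variables |
| Matching | None described | Age, gender, GHB dose and years, detoxification attempts |
| Regression on TAU per centre | Addresses which usual care was given, not who chose baclofen; linear, sensitivity only | Reports on adjunct psychological treatment are unavailable for this group |
| Correction for craving | Named for the craving analyses and for the 6-month continuer/stopper comparison, not here | Not here |

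The ANOVAs on the continuous relapse measures could be extended to take covariates, so the general covariate sentence can be honoured there. It cannot be honoured in the one test named for abstinence. Its named examples are also only socio-demographic: they do not include GHB severity, craving or psychiatric symptoms.

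**2. The plan's own sample size**

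Inputs from Sample size calculation: 70% vs 36% abstinent, multipliers 1.96 and 0.84.

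n = (1.96 + 0.84)² × (0.70 × 0.30 + 0.36 × 0.64) / 0.34² = 7.84 × 0.4404 / 0.1156 = 29.87, rounded up to 30 per group. With 25% dropout, 30 / 0.75 = 40. Both figures reproduce. The Abstract gives n = 80, which leaves 80 − 40 = 40 for TAU. The formula assumes that the groups differ only by treatment.

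**3. Illustration of scale (assumed, not from the documents)**

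Assume no baclofen effect, 36% abstinence in TAU, 40 per group, and volunteers who would have done d points better anyway. The probability that the uncorrected Pearson test gives p < 0.05 is found by summing the two binomial probabilities over all 41 × 41 outcomes with |z| ≥ 1.96:

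| d (points) | Abstinence, baclofen vs TAU | Rejection probability |
|---|---|---|
| 0 | 36% vs 36% | 4.9% |
| 10 | 46% vs 36% | 15.5% |
| 15 | 51% vs 36% | 28.6% |
| 20 | 56% vs 36% | 45.8% |

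A second route assumes one prognostic factor that is unevenly spread between the groups. With odds ratios for abstinence of 2 to 5, a 60/40 split gives a spurious difference of 3 to 7 points and rejection of 6% to 10%. A 70/30 split gives 6 to 15 points and 9% to 29%. An 80/20 split gives 10 to 23 points and 15% to 56%.

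**4. Effect of ignoring the historical matching**

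If matching were 1:1 with within-pair correlation ρ (assumed), the true null variance of the difference is (1 − ρ) times the one the Pearson test uses. The null size is then 2 × [1 − Φ(1.96 / √(1 − ρ))]: 3.9% at ρ = 0.1, 2.8% at 0.2 and 1.9% at 0.3. The test becomes conservative; it does not let confounding in.

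**5. Room for covariates**

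At the planning rates, 40 × 0.30 + 40 × 0.64 = 12 + 25.6 = 37.6, so about 38 of 80 patients are non-abstinent. A broad model (treatment, age, gender, dose, years, detoxification attempts, DDQ, VAS, DASS, MATE and six centres, hence five centre terms) has about 15 parameters: 37.6 / 15 ≈ 2.5 events per parameter. Treatment plus five covariates has 6: 37.6 / 6 ≈ 6.3. The covariate set has to be short.

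**The case against.** The authors admit the lack of randomisation, call the study explorative, and would take a positive result only as grounds for randomised trials. They promise covariates in all analyses, and an article may leave the exact adjusted model to a fuller analysis plan that is not shown. The largest suspected confounder, motivation, is not measured, so no model would remove it. All of this is fair, and it limits how serious the point is. It does not dispose of it. The article does not leave the test open: it names one that conflicts with its own covariate sentence, and the Discussion claims a protection that the concurrent comparison lacks.

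Three stronger readings are tempting, and the documents do not support them.

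- **That ignoring the matching lets confounding through.** Matching balances its variables whichever test follows. The cost is in precision and, as shown above, runs in the conservative direction. The article also does not say whether matching is individual or at group level.
- **That patients barred from baclofen become TAU controls.** This rests on one loose clause in Study design. The eligibility section speaks of participation in the study, the Discussion excludes the listed diseases from the study, and Recruitment describes TAU controls as patients who do not want baclofen. The clause needs clarifying; it does not show that ineligible patients serve as controls.
- **That 15%, 29% and 46% are the trial's false-positive rates, or what adjustment would save.** They follow from an assumed advantage that no document supplies. That advantage would come from the preference design, and adjustment would remove only its measured part.

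**Conclusion.** The point stands in limited form. The only test named for 3-month abstinence cannot hold the covariates that the plan promises, and the matching put forward against confounding applies to the historical controls alone. As written, the concurrent TAU comparison has no adjustment for measured prognostic differences. That rests on the text and needs no assumption.

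The size of the bias cannot be derived from the documents. The illustration shows only that a moderate volunteer advantage matters at this sample size: 10 points would roughly triple the nominal 5% error rate (15.5%). How much adjustment would recover depends on how much of any advantage the baseline measures capture, which is unknown. In an explorative study this is a stated method worth replacing and a claim worth correcting. It does not make the study uninformative.

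**What to change.** 1. **Main concurrent comparison.** Replace the chi-squared test with a baseline-adjusted risk difference or odds ratio with its confidence interval, from propensity-score weighting or penalised logistic regression. Prespecify a short covariate set, for example age, gender, intensity of GHB use (MATE), craving at T0 and DASS. Procedure and data collection and Table 2 show the MATE, craving and DASS measures taken at or before T0 in both concurrent groups. Add the number of detoxification attempts only if it is recorded for TAU patients; neither of those places lists it. Keep the chi-squared test as a descriptive check.
2. **Historical comparison.** Adjust for the matching variables, or use a conditional analysis if matching turns out to be individual. State which kind of matching is meant. The gain is mainly in precision.
3. **Wording.** Reconcile Study design, Recruitment and In- and exclusion criteria so that TAU controls are patients who meet the same criteria and decline baclofen. Correct the Discussion to say that matching covers only the historical group.

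The cost is redrafting and modest modelling, with no new visits or measurements for the covariates listed by name. Intervals will be somewhat wider, and unmeasured motivation remains, which the report should say.

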### Outcome and instruments

#### Primary outcome measures

The primary study outcome is the relapse rate, in other words the level of GHB use as indexed by the total number of abstinent days, the duration of continued abstinence after detoxification (CAD), time before relapse, and intensity of substance use over a period of 3 and 6 months (Timeline Follow-back Method).

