### Procedure and data collection

Patients in all treatment conditions (baclofen + TAU or TAU only) will be assessed by research assistants identically in the following time points. Before detoxification, the intensity of GHB abuse (MATE), Quality of life (EQ-5D) and psychiatric comorbidity (DASS) will be assessed. At the end of the detoxification treatment (baseline) and at follow up (three months after start of detoxification) craving (VAS, DDQ), psychiatric comorbidity (MINI plus, DASS), and Quality of life (EQ-5D) will be assessed.

The addiction physician will monitor the participants in the baclofen condition during regular medical check-ups for potential side effects (side effect checklist) and craving (VAS, DDQ), see Table 2. During the follow-up (six months after start of detoxification) the DDQ, DASS, MINI-plus, EQ-5D will be repeated. In summery self-report questionnaires will be administered at the start of detoxification; start of baclofen treatment (week 0), baclofen titration and stabilization (week 1 + 2) and maintenance treatment (week 3–12). Add to that, three months after the end of the baclofen treatment, a follow-up measurements will take place. The research assistant will build up an online Client Record Form from all the questionnaires filled in by the patients. A summary of the medical records will be added by the physician to the electronic patient file.

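### The ANOVA of the continuous GHB-use indices adjusts for no measure of prior GHB use, although patients choose between baclofen and concurrent TAU and pre-detoxification intensity is listed as measured in both groups

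*Protocol article*

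**What the plan says.** Primary outcome measures defines the primary outcome as "the level of GHB use as indexed by the total number of abstinent days", followed by duration of continued abstinence, time before relapse and intensity of use. Statistical analyses gives the method for these quantities: "ANOVA will be carried out on continuous variables, such as the total number of abstinent days, the maximum duration of continued abstinence", with time before relapse and level of use on the same list. No measure of prior GHB use appears in that model. The one covariate rule that covers every analysis reads "In all analyses socio-demographic characteristics such as age and gender will be considered as co-variates in the analysis". A further sensitivity regression deals with differences in TAU between centres.

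Study design says that assignment rests on eligibility and on the patient's own preference. Procedure and data collection says "Patients in all treatment conditions (baclofen + TAU or TAU only) will be assessed by research assistants identically", and then "Before detoxification, the intensity of GHB abuse (MATE), Quality of life (EQ-5D) and psychiatric comorbidity (DASS) will be assessed".

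Recruitment matches the historical controls on age, gender, GHB dose and years of use, and number of detoxification attempts. The Discussion presents matching on gender, age and pattern of GHB use as the means of controlling confounding. No such step is described for the concurrent TAU group.

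**The concern.** Without randomisation, nothing balances severity of GHB use between patients who accept baclofen and those who decline it. If severity predicts later use, any difference in severity passes into the estimated effect on abstinent days, continued abstinence and level of use. The direction is unknown: heavier users might be keener on medication, or less keen.

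The protocol already regards GHB dose and duration as confounders, since it matches historical controls on them. The concurrent TAU comparison, which has the better contemporaneous data, gets no equivalent protection. The covariate clause does not close the gap, because intensity of GHB use is not a socio-demographic characteristic.

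A lesser cost is precision: a prognostic covariate left out of the model stays in the residual variance.

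**Working it through.** **Inputs from the protocol article (Sample size calculation).** Two-sided alpha 0.05, 80% power, abstinence 70% versus 36%, 30 analysed per group, 25% drop-out.

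**The plan's own figure.** n = (1.96 + 0.84)² × [0.7 × 0.3 + 0.36 × 0.64] / 0.34² = 29.87, so 30 per group; 30 / 0.75 = 40 enrolled. Both reproduce and neither is disputed. They concern the abstinence rate. No sample size is given for the continuous indices, so 30 per group is carried over to them here.

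**Assumed inputs.** The document gives neither of these:
- rho, the within-group correlation between pre-detoxification intensity and the index
- delta, the difference in mean intensity between baclofen and concurrent TAU, in SD units

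**Bias of the unadjusted comparison.** If the index depends linearly on intensity, the difference in group means estimates the treatment effect plus rho × delta, in SD units of the outcome. The standard error with 30 per group is √(2/30) = 0.258 SD. The effect detectable with 80% power (t-test, 58 df) is 0.736 SD. Type I error is the rejection probability when the true effect is zero and the bias is rho × delta (noncentral t, 58 df).

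| rho | delta (SD) | bias (SD) | share of 0.736 SD | type I error |
|---|---|---|---|---|
| 0.2 | 0.25 | 0.05 | 7% | 5.4% |
| 0.5 | 0.3 | 0.15 | 20% | 8.8% |

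**Precision.** Adding the covariate multiplies the residual variance by 1 − rho². The standardised effect becomes 0.736 / √(1 − rho²), tested on 57 df. Groups are taken as balanced on the covariate.

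| rho | variance factor | power | gain over 80% |
|---|---|---|---|
| 0.1 | 0.99 | 80.4% | 0.4 points |
| 0.2 | 0.96 | 81.6% | 1.6 points |
| 0.3 | 0.91 | 83.5% | 3.5 points |
| 0.36 | 0.87 | 85.1% | 5.1 points |
| 0.5 | 0.75 | 89.9% | 9.9 points |

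The gain is below 2 points up to rho 0.2 and reaches 5 points only near rho 0.36.

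**The case against.** **The indices have no baseline.** Abstinent days and continued abstinence are counted from the end of detoxification, when every patient has stopped. They come from the Timeline Follow-back, which Table 2 schedules only at weeks 12 and 24. MATE is another instrument, applied during active dependence. This stands: pre-detoxification intensity is a prognostic covariate and nothing more.

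**The craving analysis is not a true parallel.** A reader might infer that the plan contradicts itself, because craving is "corrected for craving levels immediately after detoxification" while GHB use is not. The document does not support that. Craving is measured by the same scales at the end of detoxification and at 3 months, so it has a real baseline. Correcting outcomes that have one, and not those that lack one, is consistent.

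**Availability is not certain.** Additional measures describes MATE section 1 as a record of other substances. Recruitment has the research nurse give further study information, and consent follow, after detoxification. Table 2's week 0 is the end of detoxification, so its mark for both groups ("xx = baclofen group and control group TAU only") does not itself prove a pre-detoxification measurement. Procedure and data collection nevertheless lists that measurement for both conditions. The gap is one to confirm, not a reason to leave the covariate out.

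**The size is assumed.** This also stands. Among the reported reasons for relapse in the Background, prior dose does not appear, so a small rho is plausible. With 70% and 36% expected to be abstinent, abstinent days will also pile up at the maximum, and normal-theory power is then only a rough guide.

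**The article is condensed and the study calls itself explorative.** Full covariate lists are often left to a later document. Here, though, the article states both the method for these indices and the covariate rule for all analyses. The change is to that stated choice.

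**Conclusion.** The point holds for the baclofen versus concurrent TAU comparison of abstinent days, continued abstinence and level of use, and it rests mainly on confounding. A factor that the protocol itself treats as a confounder is left unaddressed in a comparison formed by patient preference. The size cannot be fixed from the document: it runs from negligible at rho 0.2 with a 0.25 SD difference to about a fifth of the detectable effect at rho 0.5 with 0.3 SD. These figures assume a linear relation and 30 analysed per group.

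Two stronger readings are not supported. A reader might infer that a substantial loss of power has been shown, but that needs a correlation of about 0.36 or more, which nothing in the document establishes. A reader might also extend the bias to the historical comparison, but those controls are already matched on GHB dose and years.

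**What to change.** In Statistical analyses, for baclofen versus concurrent TAU at 3 months, replace the ANOVA of abstinent days, continued abstinence and level of GHB use by ANCOVA (linear regression on group). Prespecify pre-detoxification GHB intensity (MATE), age and gender as covariates, instead of leaving covariates to be considered. Report the unadjusted ANOVA as a sensitivity analysis. Confirm first that MATE intensity before detoxification is recorded for GHB itself in both concurrent groups.

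For the historical comparison, matching already addresses GHB dose and years. The matching variables may be added as covariates, but they should not be presented as the same measure as MATE.

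The cost is a change of wording and one or two degrees of freedom for the added covariate. If the measurement is in place as listed, no new data are needed. The adjustment does not remove confounding by unmeasured reasons for choosing or declining baclofen, and the report should say so.

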### Aims and hypotheses

The primary aim of the current study is to assess the potential of baclofen to prevent relapse in recently detoxified GHB-dependent patients. We hypothesize that administration of baclofen to GHB-dependent patients after detoxification is associated with decreased relapse rates as compared to treatment as usual (without baclofen). We also hypothesize that treatment with baclofen is associated with reduced levels of craving for GHB and reduced psychiatric symptoms levels, including anxiety, and increased quality of life. We expect baclofen treatment to cause minimal side effects in these patients. Finally, we expect a lower drop-out rate from adjuvant therapy (TAU) in the intervention group.

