#### Sample size calculation

To date, there are no published studies on the effect of baclofen on relapse in GHB dependent patients. Therefore, we used the results of previous studies on the effect of baclofen in alcohol dependent patients and our previous work on GHB dependence, in order to estimate the required sample size. Two RCTs showed that baclofen was superior to placebo in increasing abstinence rates in alcohol dependent patients: 70% (14 out of 20) versus 21% (4 out of 19) within a period of 30 days [29] and 71% (30 out of 42 p) versus 29% (14 out of 42) within a period of 12 weeks [30]. These results indicate a potential increase in abstinence of 42–49% with baclofen treatment for alcohol dependence. Results of the previous national GHB project stated that 36% of the patients succeeded to avoid relapse in GHB within a period of 3 months after detoxification without any medical interventions [20]. Therefore, we will consider a percentage of importance difference in baclofen effect in the GHB dependent participants of 34% between the Baclofen + TAU group and the TAU only or the matched control group with an expected abstinence rate with baclofen of 70% as in the alcohol studies and of 36% without baclofen.

We used the following formula comparing two proportions to calculate the sample size, n = [(Zα/2 + Zβ)^2^ × {(p1 (1-p1) + (p2 (1-p2))}] / (p1 - p2)^2^, n = [(1.96+ 0.84)^2^ × {(0.7 (1–0.7) + (0.36 (1–0.36))}] / (0.34)^2^, according to [name] sample size calculator, Exeter Initiative for Statistics. The calculation estimates that the minimal total samples size of 30 patients per group would be sufficient to detect a clinical difference of 34% in two-tailed z-test of proportions (α = 0.05, β=0.80). In the alcohol studies and our previous work with GHB inpatients an attrition rate of 13–15% was reported. We anticipate a slightly higher drop-out rate of 25%, due to the outpatient component of the baclofen treatment. Therefore we will include 40 participants in the baclofen treatment group.

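### Time before relapse, one of several listed primary indices, is assigned to ANOVA although about half of patients are expected to have no relapse by 3 months

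*Protocol article*

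**What the plan says.** Under Primary outcome measures, the protocol article indexes the primary outcome by total abstinent days and by "the duration of continued abstinence after detoxification (CAD), time before relapse, and intensity of substance use over a period of 3 and 6 months". Under Statistical analyses it fixes the method: "ANOVA will be carried out on continuous variables, such as the total number of abstinent days, the maximum duration of continued abstinence, time before relapse". The same sentence defines the event ("relapse defined as ≥ 3 times GHB use per day, for 2 subsequent days") and sets a 3-month window. No time-to-event method is named, and nothing says what value a patient without a relapse receives.

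The dichotomous abstinence rate has its own Pearson chi-squared test, and numbers maintaining abstinence are to follow intention-to-treat principles.

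The Sample size calculation section gives the rates: "expected abstinence rate with baclofen of 70% as in the alcohol studies and of 36% without baclofen". The control figure is a 3-month relapse-free share: "36% of the patients succeeded to avoid relapse in GHB within a period of 3 months after detoxification". Drop-out is put at 25%. Table 2 schedules Timeline Follow-back at week 12 in both groups and at week 24 in the baclofen group only.

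**The concern.** A patient who has not relapsed when observation ends has no relapse time, only a lower bound for one. The same holds for continued abstinence when it is counted from the end of detoxification. ANOVA compares means of fully observed values, so such a patient must be left out or given a number. The results section would then report a mean time before relapse whose meaning depends on a scoring decision that the plan does not make. By the plan's own rates this affects about half of the patients, and very unequally by group.

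At stake are lost power under a reasonable scoring and, under poor scorings, either an effect that is hidden or a false one produced by unequal drop-out.

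**Working it through.** **Inputs from the protocol article.** Relapse-free at 3 months: 70% and 36%. Two-sided α 0.05 with Z values 1.96 and 0.84. Drop-out 25%. Baclofen group 40, total 80.

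**Assumptions added here.** 40:40 split; exponential relapse times; window of 84 days (week 12); drop-out unrelated to relapse. The hazards are set to reach 70% and 36% at the end of the window, so its exact length (84 or 90 days) rescales the times but does not change the power.

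**1. The plan's own figure.** (1.96 + 0.84)² × (0.70×0.30 + 0.36×0.64) / 0.34² = 7.84 × 0.4404 / 0.1156 = 29.87, so 30 per group; 30 / 0.75 = 40. It reproduces. It concerns the dichotomous rate only.

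**2. Patients without a relapse time.** 0.70×40 + 0.36×40 = 28 + 14.4 = 42.4 of 80, or 53%. With a matched historical group of 40 (its size is not stated) at 36%: 56.8 of 120, or 47%. The analysis definition of relapse is looser than any use, so the true shares could be higher.

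**3. What each scoring does to the means.** h = −ln(S)/84, so 1/h = 235.5 days (baclofen) and 82.2 days (TAU). The hazard ratio is ln(0.70)/ln(0.36) = 0.349.
- Non-relapsers set to 84 days: mean (1 − S)/h = 0.30×235.5 = 70.7 versus 0.64×82.2 = 52.6, a difference of about 18 days.
- Relapsers only: mean 1/h − 84·S/(1 − S) = 235.5 − 196.0 = 39.5 versus 82.2 − 47.25 = 35.0, a difference of 4.5 days.

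**4. Simulated power, 40 per group** (2,000 to 3,000 trials per scenario; Monte Carlo error about √(0.8×0.2/2000) = 0.9 points per figure).

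| Handling | ANOVA | Log-rank |
|---|---|---|
| No drop-out, non-relapsers set to end of window | 80% | 88% |
| 25% drop-out, drop-outs missing, other non-relapsers set to end of window | 68% | 77% |
| 25% drop-out, last-contact times entered as relapse times | 62% | 84% |
| Relapsers only | 8–9% | not applicable |

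In the third row the log-rank test treats the last-contact times as censored.

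**5. False positives with no effect** (36% relapse-free in both groups, assumed drop-out splits).
- Last-contact times entered as relapse times: ANOVA rejects about 14% at 25% versus 0% drop-out and 20% at 40% versus 10%. A repeat gave 13% and 16%. Log-rank stays near 5%.
- Drop-outs missing: ANOVA rejects 5–6%, so the inflation disappears.

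**The case against.** The strongest defence is that completers can be scored at the length of the window. Mean relapse-free days over a fixed window is an interpretable restricted mean, fully observed for completers, and ANOVA on it costs little. This stands as far as it goes: it is the 80% versus 88% case. It weakens once some patients are lost before the window ends, and the plan expects 25% drop-out.

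Three stronger readings are tempting and are not supported.
- *Most patients never relapse.* This is true of the baclofen group (70%), false for TAU (36%), and a bare 53% overall at 40:40.
- *The plan discards non-relapsers or counts them as relapsed at last contact.* The article states neither scoring. The relapsers-only power, the 62% and the raised false-positive rates are therefore illustrations.
- *Differential drop-out will bias the result.* The Aims section says "we expect a lower drop-out rate from adjuvant therapy (TAU) in the intervention group". That concerns leaving therapy, not loss to outcome assessment. The unequal splits above are assumed, and the inflation also needs last-contact scoring. Because Timeline Follow-back falls only at week 12 within the first three months, an early drop-out may simply be missing.

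It is also fair that the sample size rests on the chi-squared comparison, that time before relapse is one of several indices, and that the authors call the study explorative.

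**Conclusion.** The point holds in a limited form. The article fixes a method that does not suit a right-censored variable that it lists among its primary indices. Under the most reasonable scoring the cost is about 8 to 9 points of power. Under scorings that the text leaves open but does not state, the cost could be much larger: power of about 62% or below 10%, or false positives of about 14–20% with unequal drop-out.

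These sizes rest on exponential times, a 40:40 split, the plan's 70% and 36% read as relapse-free shares, and drop-out independent of relapse. The ordering, with log-rank ahead of every ANOVA scoring, was the same in all scenarios run. The abstinence-rate comparison is untouched, so this should be corrected before analysis but does not invalidate the main test.

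**What to change.** In Statistical analyses, take time before relapse off the ANOVA list and analyse it by Kaplan-Meier curves, a log-rank test and a Cox model adjusted for baseline confounders. Do the same for continued abstinence where it means the period from the end of detoxification ("the duration of continued abstinence after detoxification (CAD), time before relapse"). If the maximum duration in the analysis section means the longest spell at any time, it is a different quantity, and the article should say which is meant.

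State the origin as T0, the end of detoxification. Censor at the end of the 3-month window or, for patients lost earlier, at the last date on which they are documented relapse-free. Apply the rule identically in both groups. This needs care because Timeline Follow-back comes only at week 12 and Table 2 marks the interim medical consults for the baclofen group alone.

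The cost is small. It is a change of wording plus one rule for early drop-outs, and SPSS, the named package, has the procedures. Two limits remain. Patients lost before any documented date contribute little or nothing. With about 40 × (0.30 + 0.64) = 37.6 relapses expected, before any loss to drop-out, the Cox model can carry only a few covariates.
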